## Abstract

**Background:**

There is emerging evidence of the central role of neutrophils in both atherosclerotic plaque formation and rupture. Patients with lower neutrophil counts following acute coronary syndromes tend to have a greater coronary flow reserve, which is a strong predictor of long-term cardiovascular health. But so far, no data are available regarding the impact of neutrophil inhibition on cardiovascular clinical or surrogate endpoints. Therefore, the aim of this study is to investigate the effects of AZD5069, a cysteine-X-cysteine chemokine receptor 2 (CXCR2) inhibitor, on coronary flow reserve and coronary structure and function in patients with coronary artery disease.

**Methods/Design:**

Ninety subjects with coronary artery disease undergoing percutaneous coronary intervention will be included in this investigator-driven, randomised, placebo-controlled, double-blind, phase IIa, single-centre study. Participants will be randomised to receive either AZD5069 (40 mg) administered orally twice daily or placebo for 24 weeks. Change in coronary flow reserve as determined by ^13^N-ammonia positron emission tomography-computed tomography will be the primary outcome. Change in the inflammatory component of coronary plaque structure and the backward expansion wave, an invasive coronary physiological measure of diastolic function, will be assessed as secondary outcomes.

**Discussion:**

Cardiovascular surrogate parameters, such as coronary flow reserve, may provide insights into the potential mechanisms of the cardiovascular effects of CXCR2 inhibitors. Currently, ongoing trials do not specifically focus on neutrophil function as a target of intervention, and we therefore believe that our study will contribute to a better understanding of the role of neutrophil-mediated inflammation in coronary artery disease.

**Trial registration:**

EudraCT, 2016-000775-24. Registered on 22 July 2016.

International Standard Randomised Controlled Trial Number, ISRCTN48328178. Registered on 25 February 2016.

**Electronic supplementary material:**

The online version of this article (doi:10.1186/s13063-017-2210-2) contains supplementary material, which is available to authorized users.

## Background

Atherosclerosis, the principal cause of myocardial infarction and stroke, is a progressive inflammatory disease characterised by the accumulation of lipids and fibrous elements in large arteries [1]. Being an inflammatory disease, atherosclerosis involves recruitment of leucocytes (predominantly neutrophils and monocytes) to sites of vascular injury. Typically, this is triggered by the accumulation of oxidised low-density lipoprotein (LDL) within the intima, which stimulates endothelial cells to express an atherosclerotic phenotype and leads to the adherence of leucocytes on their surface. These inflammatory cells transmigrate into the intima, where monocytes proliferate and differentiate into macrophages which take up oxidised LDL, forming foam cells [1].

Atherosclerotic plaques exhibit two major phenotypes: (1) stable plaques, characterised by a thick fibrous cap separating a relatively small lipid core from the lumen, which are associated with a low risk of thrombotic complications; and (2) unstable plaques, characterised by a large lipid core covered by a thin fibrous cap prone to rupture and thrombus formation and associated with a higher risk of thrombotic complications [2, 3]. Leucocytes—in particular neutrophils and monocytes—are involved both in atherogenesis and in plaque destabilisation, the latter especially so for neutrophils [4, 5]. Specifically, neutrophils are over-represented in the vasculature of patients with unstable atherosclerotic plaque [4] and are associated with histologic features of plaque vulnerability [5, 6]. In addition to these established structural changes, a high-fat meal has been shown to elicit a mild neutrophilia along with endothelial dysfunction [7]. In recent studies, colchicine, a known neutrophil chemotaxis inhibitor, has been shown to reduce vascular events in patients with coronary heart disease [8].

The control of migration of neutrophils into coronary plaque is not fully understood, but it is thought to involve cysteine-X-cysteine chemokine receptor 2 (CXCR2) [9]. This G protein-coupled receptor binds interleukin-8 (IL-8) with high affinity together with chemokine (C-X-C motif) ligands 1, 2, 3 and 5 (CXCL1, CXCL2, CXCL3 and CXCL5, respectively). CXCR2 is expressed at a high level in neutrophils and plays a crucial role in mediating neutrophil migration, such that its inhibition greatly decreases neutrophil recruitment to sites of inflammation [10, 11]. In previous studies, AZD5069, a specific CXCR2 antagonist, was found to be potent in inhibiting calcium flux, chemotaxis and CD11b expression on human neutrophils in vitro in response to the CXCR2 ligands IL-8 and growth related oncogene-α [12]. In a rodent lipopolysaccharide (LPS) challenge model of pulmonary inflammation, AZD5069 reduced LPS-induced neutrophilia in a dose-dependent manner in both bronchial fluid and serum [13].

Because neutrophil recruitment into atherosclerotic plaques plays a crucial role in plaque destabilisation and vascular inflammation, it is possible that CXCR2 inhibition will give rise to improved coronary endothelial function, which will be reflected in an improvement in total coronary flow reserve (CFR). CFR is an integrated measure of coronary artery status encompassing both macro- and microvascular function, and it has prognostic value over and above other markers of cardiovascular risk [14]. Therefore, improvement in CFR with CXCR2 inhibition would be expected to translate into prognostic benefits clinically in long-term follow-up.

In addition to the effects on coronary flow dynamics, decreased neutrophil recruitment may also translate into a reduction in the high-risk morphologic features of coronary plaque (visualised by virtual histology intravascular ultrasound [VH-IVUS] as a diminution in size of the necrotic core of lesions). Additionally, there is evidence that neutrophil infiltration is involved in the pathophysiology of restenosis following coronary angioplasty [15, 16].

Therefore, in the CXCR2 Inhibition – a novel approach to treating CoronAry heart DiseAse (CICADA) study, we aim to perform a randomised, placebo-controlled, double-blind trial to investigate the effect of the CXCR2 inhibitor AZD5069 on CFR and coronary plaque morphology. This will help to improve understanding of the cardiovascular effects of CXCR2 inhibition in patients with coronary artery disease (CAD).

## Methods

### Design

This is a prospective, randomised, placebo-controlled, double-blind, phase IIa, single-centre study to evaluate the effect of the CXCR2 antagonist AZD5069 40 mg twice daily on cardiovascular surrogate measures in patients with CAD undergoing percutaneous coronary intervention (PCI). The trial was approved by the South Central - Berkshire B Research Ethics Committee (16/SC/0478) and is to be conducted at the Department of Cardiology, St. Thomas’ Hospital, London, UK. The study is co-sponsored by King’s College London and Guy’s and St. Thomas’ NHS Foundation Trust.

All participants will be asked to provide written informed consent before entering the study. Clinical trial authorisation has been obtained from the Medicines and Healthcare Products Regulatory Agency (MHRA) (EudraCT, 2016-000775-24). A certificate for the administration of radioactive medicinal products has been granted by the UK Administration of Radioactive Substances Advisory Committee (ARSAC) (RPC 261/3492/35652). Important protocol modifications will be reported to the South Central - Berkshire B Research Ethics Committee and, if necessary, to the MHRA and ARSAC. This study follows the international recommendations for interventional trials (*see* Fig. 1 and the Standard Protocol Items: Recommendations for Interventional Trials [SPIRIT] checklist in Additional file 1).

**Fig. 1 Fig1:**
[figure not shown]
Standard Protocol Items: Recommendations for Interventional Trials (SPIRIT) figure for the CXCR2 Inhibition – a novel approach to treating CoronAry heart DiseAse (CICADA) trial, outlining schedule for enrolment, intervention and assessments. *ECG* Electrocardiogram, *hs-CRP* High-sensitivity C-reactive protein, *MPA* Monocyte-platelet aggregates, *PET* Positron emission tomography

### Primary objective

The primary objective of this trial is to determine, in patients undergoing PCI for atherosclerotic coronary disease, if 24 weeks of CXCR2 inhibition therapy will give rise to improvement in CFR as measured by ^13^N-ammonia positron emission tomography-computed tomography (PET-CT) compared with placebo.

### Secondary objective

The secondary objectives of the study are to ascertain, in patients undergoing PCI for atherosclerotic coronary disease, if 24 weeks of CXCR2 inhibition therapy will result in a reduction in the inflammatory component of coronary plaque, a decrease in the degree of in-stent restenosis and improvements in coronary microvascular function compared with placebo.

### Inclusion and exclusion criteria

Participants in the trial will be aged ≥ 18 years, have angiographically proven coronary heart disease, be undergoing native-vessel PCI, and have a persistent neutrophil count > 4.0 × 10^9^/L. Otherwise, they will be receiving the standard of care for ischaemic heart disease (including appropriate antiplatelet therapy, statin, and/or antihypertensives as clinically indicated).

The exclusion criteria are as follows: acute ST-elevation myocardial infarction, prior cardiovascular surgery, known active or recent infection, evidence of tuberculosis, known immunocompromised state or history of organ transplantation, known major organ dysfunction or other significant co-morbidity, use of a cytochrome P450 3A4 inhibitor and inducers, alanine aminotransferase or aspartate aminotransferase level ≥ 2.5 times the upper limit of normal, QTc > 450 milliseconds for males and >470 milliseconds for females, pregnancy or breastfeeding during the study, women of childbearing potential not using a highly effective method of contraception, and unwilling or unable to give informed consent.

### Eligibility and recruitment

The study population will consist of 90 subjects with CAD undergoing PCI. Subjects are identified from inpatient admissions and outpatient angioplasty waiting lists at St. Thomas’ Hospital, London, UK. The direct care team staff will inform patients about the possibility of being enrolled in this study. No study-related procedures are undertaken before obtaining informed consent. A member of the study team will explain the study procedures in detail and provide the participant with a patient information sheet. After a minimum of 2 h, but ideally more than 24 h, the participant will be asked about their willingness to participate in this research study, and any questions will be clarified. After informed consent is obtained, participants will be given a copy of the informed consent form to sign and assigned a screening identification number.

### Screening

Screening of participants consists of the evaluation of inclusion and exclusion criteria. After informed consent is obtained by a member of the trial team, an electronic case report form (eCRF) is created for potential participants, including information about medical history, physical examination and their current medications. Women of childbearing potential undergo urine pregnancy testing.

### Participant timeline

If eligible, subjects are scheduled for the following study visits (Fig. 1). Patients undergo invasive coronary angiography with PCI as per normal clinical care, but they will also undergo IVUS to provide greyscale and virtual histology of all major coronary arteries. Patients with suitable coronary anatomy will be invited to have invasive assessment of coronary and microvascular physiology under adenosine-induced hyperaemia (using a ComboWire; Volcano Corp., Rancho Cordova, CA, USA).

Four weeks later, subjects will re-attend the cardiology department, at which time a full history and physical examination will be performed and inclusion criteria confirmed. Assessments will include a 12-lead electrocardiogram, as well as blood tests (fasted) for blood count and biochemistry (renal, liver, lipid, glycaemic and thyroid profiles) and high-sensitivity C-reactive protein (hs-CRP) and homocysteine levels. Screening blood tests for disorders which may exclude patients from the study will be drawn as indicated (e.g., serum hepatitis B surface antigen, hepatitis C antibody, and HIV testing if prompted by history). Additionally, an aliquot of blood will be taken for measurement of circulating monocyte-platelet aggregates (MPAs, a highly sensitive and reproducible index of degree of platelet activation) by flow cytometry. In the case of women of childbearing potential, pregnancy will be excluded by performing a pregnancy test on a spot urine. Once eligibility has been confirmed, ^13^N-ammonia PET-CT cardiac scans will be obtained at rest and during adenosine-induced hyperaemia to measure CFR. The CT scan will be obtained prior to the PET scan for attenuation correction at rest and stress, and prior to the rest scan, the CT scan will also be used to measure calcium score.

After randomisation, subjects will be allocated 2:1 to receive either AZD5069 or matched placebo, orally, for the succeeding 24 weeks. At different time points (weeks 1, 2, 4, 8, 12, 16, 20 and 24), patients will attend for repeat visits, at which time they will undergo a physical examination and have a blood sample taken for the purpose of determining safety and efficacy biomarkers. At weeks 1, 12 and 24, patients will attend prior to their morning dose, and additional blood samples will be taken for the purpose of measuring plasma drug levels. At weeks 4, 8, 12, 16, 20 and 24, spot urine samples will be obtained from women of childbearing potential in order to exclude pregnancy; if they have a positive test result at any point, they will be immediately withdrawn from the study. At week 24, a repeat ^13^N-ammonia PET scan will be obtained to assess change from baseline in total CFR, and at the same time point, repeat coronary angiography together with IVUS will be performed to assess change in plaque composition and degree of restenosis. Those patients who initially had a ComboWire assessment will be invited to have a repeat assessment at the time of their repeat coronary angiography. A flow diagram of the protocol is shown in Fig. 2.

**Fig. 2 Fig2:**
[figure not shown]
Flowchart of CXCR2 Inhibition – a novel approach to treating CoronAry heart DiseAse (CICADA) trial protocol. Flowchart depicts the study process and patient visit details for enrolled candidates in the CICADA study. *PCI* Percutaneous coronary intervention, *PET* Positron emission tomography, *IVUS* Intravascular ultrasound

### Outcome measurements

The primary outcome is the change in total CFR from baseline, as measured by ^13^N-ammonia PET, before and after 24 weeks of treatment with AZD5069 or matched placebo. The secondary endpoints are as follows:Change in plaque composition, as measured by VH-IVUS, before and after 24 weeks of treatment with AZD5069 or matched placeboDegree of in-stent restenosis, as measured by IVUS, before and after 24 weeks of treatment with AZD5069 or matched placeboChange in the magnitude of the backward expansion wave (BEW), as measured by ComboWire assessment, before and after 24 weeks of treatment with AZD5069 or matched placebo

### Randomisation and blinding

Participants will be randomised to one of the two study arms (AZD5069 versus placebo) in a 2:1 ratio in real time by using the web-based randomisation service provided by the King’s Clinical Trials Unit. The randomisation system is programmed to use block randomisation with randomly selected block sizes. The randomisation system sends unblinded treatment allocation codes to the pharmacy department at Guy’s and St. Thomas’ NHS Foundation Trust and the Emergency Scientific and Medical Services (ESMS).

The pharmacy department will use treatment allocation to dispense appropriate study medication or matched placebo. The labels of the study medication display the name of the trial, the name of the investigational medicinal product and contact details of the principal investigator.

A 24-h emergency code break and medical information service will be provided by ESMS staff, who are not involved as study investigators. Each randomised subject will be provided with a card detailing code break telephone numbers and emergency contact details. Subjects will be requested to carry this card with them at all times whilst participating in the trial.

### Interventions

The subjects will receive either AZD5069 40 mg or matched placebo tablets administered orally twice daily for 24 weeks. The drug and placebo are manufactured by AstraZeneca (London, UK). The drug product is presented as plain, round, beige, film-coated tablets packaged in bottles. The tablets contain mannitol, microcrystalline cellulose, croscarmellose sodium, sodium lauryl sulphate, sodium stearyl fumarate, polyvinyl alcohol, titanium dioxide, polyethylene glycol, talc, iron oxide yellow, iron oxide red and black iron oxide. Matching placebo tablets are identical in appearance and tasteless. The pharmacy department at Guy’s and St. Thomas’ NHS Foundation Trust packs the medication as 2- to 4-week supplies for study participants and labels the study medication per current regulatory requirements.

At each visit, pill counts will be conducted to verify medication adherence. Significant non-adherence is defined as missing 20% or more doses of trial medication during the treatment period. In the case of study medication non-compliance, participants will continue to be followed to their last visit. These data would not be part of the per-protocol analysis but would form part of an intention-to-treat analysis.

Any investigational medicinal product, dispensed and unused or not dispensed, will be disposed of by the pharmacy department at Guy’s and St. Thomas’ NHS Foundation Trust. Withdrawal of consent and major protocol violations will lead to an early study termination for the subject.

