### Withdrawal of subjects

The study drug must be discontinued if any of the following occur:An exclusion criterion is incident during the study.Absolute neutrophil count < 1 10^9^/L is noted in two consecutive samples within 48 h.The participant misses > 20% of his or her doses.The participant decides he or she no longer wishes to continue.It is recommended by the investigator.

Participants have the right to withdraw from the study at any time for any reason. The investigator also has the right to withdraw patients from the study drug in the event of inter-current illness, adverse events (AEs), serious adverse events (SAEs), suspected unexpected serious adverse reactions (SUSARs), protocol violations, cure, or administrative or other reasons. It is understood by all concerned that an excessive rate of withdrawals can render the study un-interpretable; therefore, unnecessary withdrawal of patients should be avoided. Should a patient decide to withdraw from the study, all efforts will be made to report the reason for withdrawal as thoroughly as possible. Should a patient withdraw from study drug only, efforts will be made to continue to obtain follow-up data with the permission of the patient. Participants who wish to withdraw from trial medication will be asked to confirm whether they are still willing to provide the following:Trial-specific data at subsequent scheduled visitsClinical follow-up data collected as per routine clinical practice

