A secondary outcome is the change in the magnitude of the BEW, a key component of the coronary wave profile, with maximal hyperaemia. From previous work, we expect the magnitude of the BEW to increase 40% with adenosine induced maximal hyperaemia in patients with CAD. Unpublished data from the host centre suggest that in patients without CAD, the BEW can increase a further 14%. Assuming an α error probability of 0.05 (two-tailed), power 0.80 and allocation ratio 2:1 (active drug to placebo), power calculation (using G*Power 3.1.3 software) indicates that we would need 26 subjects in the active and 13 subjects in the placebo group. The BEW measurement has a standard deviation of 21%, as such we will need to recruit 57 patients in total to undergo ComboWire assessment as part of their invasive protocol.

A full description of the statistical analysis plan is beyond the scope of this protocol, and will be published separately. In summary, the primary analysis will be an intention to treat analysis. An analysis of covariance model will be used to obtain an estimate for the mean difference in total CFR between the two treatment groups including covariates for baseline CFR. The estimated treatment effect will be reported with 95% confidence intervals and corresponding *p* value.

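### Ending study participation for major protocol violations other than medication non-compliance forgoes the week-24 PET that the intention-to-treat primary analysis needs

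*Protocol article*

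**What the plan says.** Three sections of the protocol article bear on this.

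- **Interventions.** On adherence: "In the case of study medication non-compliance, participants will continue to be followed to their last visit". On the use of those data: "These data would not be part of the per-protocol analysis but would form part of an intention-to-treat analysis". The next paragraph then sets a different rule for another group: "Withdrawal of consent and major protocol violations will lead to an early study termination for the subject".
- **Withdrawal of subjects.** Protocol violations appear in a list of reasons for which the investigator may take a patient off study drug. The section goes on: "Should a patient withdraw from study drug only, efforts will be made to continue to obtain follow-up data", subject to the patient's permission.
- **Statistics and sample size calculation.** The article states that "the primary analysis will be an intention to treat analysis". On the model: "An analysis of covariance model will be used to obtain an estimate for the mean difference in total CFR between the two treatment groups", with baseline CFR as covariate.

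On timing, the Participant timeline section says: "At week 24, a repeat ^13^N-ammonia PET scan will be obtained to assess change from baseline in total CFR". It describes no other PET after baseline and no scan at early termination.

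**The concern.** An intention-to-treat analysis needs outcomes from participants as randomised, including those who later depart from the protocol. The termination sentence is mandatory, and it ends study participation rather than study drug. It treats a protocol violation like withdrawal of consent, although only the latter obliges the trial to stop collecting data.

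CFR by PET is measured once after baseline, so termination before week 24 removes the primary outcome altogether. The repeat IVUS and ComboWire assessments, due at the same time point, go with it. The separate analysis plan can say how missing values are handled, but it cannot recover scans that the protocol stopped obtaining, and there is no interim PET CFR to support imputation.

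A violation happens after randomisation. If its frequency, or the outcome of those who commit it, differs by arm, the participants left for analysis are no longer the randomised comparison.

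**Working it through.** **1. What happens to each type of participant, as written**

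| Situation | Section | Follow-up | Week-24 PET |
|---|---|---|---|
| Medication non-compliance | Interventions | Continues to last visit | Expected; enters the ITT analysis |
| Withdrawn from study drug only (protocol violations are a listed reason) | Withdrawal of subjects | Sought, with permission | Sought |
| Major protocol violation | Interventions | Study terminated early | None, if terminated before week 24 |
| Withdrawal of consent | Interventions | Study terminated early | None; a legitimate end to data collection |

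The third row is the conflict. The missing scan is an inference from the termination rule and the single week-24 scan; the article does not say it outright. The article does not define a major violation. Substantial non-adherence might also be classed as one, in which case rows 1 and 3 would give opposite instructions for the same person.

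**2. The plan's own sample size**

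Inputs (Statistics and sample size calculation): d = 0.7, two-sided α = 0.05, power 0.80, allocation 2:1; stated requirement 51 + 25 = 76; planned recruitment 60 + 30 = 90.

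For a two-sample t test, the noncentrality is d × √(n₁n₂/(n₁+n₂)) on n₁+n₂−2 degrees of freedom. For 51/25 this is 0.7 × √(1275/76) = 2.87, which gives power 0.808. The stated figure reproduces.

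**3. Power under equal proportional loss in both arms** (loss rates are assumptions; d = 0.7)

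| Loss | Active/placebo | Noncentrality | Power |
|---|---|---|---|
| 0% | 60/30 | 0.7 × √20 = 3.13 | 0.872 |
| 10% | 54/27 | 0.7 × √18 = 2.97 | 0.835 |
| 20% | 48/24 | 0.7 × √16 = 2.80 | 0.789 |

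It takes 90 − 76 = 14 losses (14/90 = 15.6%) to come down to the stated requirement. The article justifies those 14 extra participants by smaller effect sizes and by stratification on plasma drug level, not by expected losses.

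**4. Bias under loss from the active arm only** (all inputs are assumptions)

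Let p be the share of the active arm removed, and Δ the difference in mean outcome between those retained and those removed. The full-arm mean is (1−p) × retained mean + p × removed mean. Using only the retained participants therefore shifts the arm mean by p × Δ.

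- Low: 0.10 × 0.5 SD = 0.05 SD, and 0.05/0.7 = 7% of the planned effect.
- High: 0.15 × 1.0 SD = 0.15 SD, and 0.15/0.7 = 21% of the planned effect.

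With loss in both arms, the bias is p(active) × Δ(active) − p(placebo) × Δ(placebo). It is zero when shares and differences are equal.

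**The case against.** The strongest reply is that the article protects the largest group at risk. A reader might infer that the termination rule turns the primary analysis into one of compliant participants. The documents do not support that: the Interventions section expressly keeps medication non-compliers in follow-up and in the intention-to-treat analysis. What remains is the set of other major violations, undefined in the article and possibly small. A violation discovered at or after week 24 would cost no scan.

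Second, some obvious treatment-related examples may fall under a different rule. Active infection and use of a CYP3A4 inhibitor or inducer are exclusion criteria, and the Withdrawal of subjects section answers an exclusion criterion arising during the study by discontinuing study drug. The route to differential loss through the termination sentence is therefore possible but not demonstrated.

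Third, the two sections can be read as graded: discretionary withdrawal from drug for any violation, mandatory termination for a major one. Follow-up under the Withdrawal section is also only an effort that depends on permission. So the clash between these two sections is arguable.

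These replies narrow the point but do not remove it. Even on the graded reading, the mandatory rule ends data collection for randomised participants because of a post-randomisation event, and that conflicts with the declared intention-to-treat analysis.

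**Conclusion.** The point holds in a limited form. For major protocol violations other than medication non-compliance, the Interventions section requires early termination. Before week 24 this forgoes the primary outcome that the intention-to-treat analysis calls for. It also sits badly with the Withdrawal of subjects section.

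The size is unknown, because the article gives no violation rate. The 0.05–0.15 SD bias is an illustration that rests on one-sided loss of 10–15% and an outcome difference of 0.5–1 SD; it should not be read as an estimate. Nor do the documents support a claim that the rule leaves the trial underpowered: at d = 0.7, power stays above 0.80 at 10% equal loss and drops just below it at 20%. The bias and power figures describe different scenarios and should not be combined. The possible bias matters more than the lost power, because extra recruitment would not correct it.

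**What to change.** Reconcile the Interventions, Withdrawal of subjects and Statistics sections by separating the end of study drug from the end of follow-up:

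- A major protocol violation removes the participant from the per-protocol set but does not by itself end follow-up.
- The week-24 PET is still sought, with the participant's consent and where the protocol's safety-based withdrawals (for example, the study withdrawal after a positive pregnancy test in the Participant timeline section) do not preclude it.
- The result is analysed in the arm to which the participant was randomised.
- Withdrawal of consent for further data continues to end data collection.

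This changes data collection only and leaves the rules on stopping study drug as they are. The cost is protocol wording, plus week-24 scans that are already in the visit schedule. The article reports recruitment as ongoing, so the change can still save scans not yet due; scans already forgone cannot be recovered.
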